## **10.3 SAE notification procedure**

CTRU should be notified of all SAEs (unless exempt), within 24 hours of the investigator becoming aware of the event.

The SAE form must be completed by the investigator or delegated member of the research team. All SAE forms must be sent by email to [[contact]](mailto:[contact]). Receipt of the initial report should be confirmed within one working day. The site research team should contact the study team at CTRU if confirmation of receipt is not received within one working day.

Initial SAE reports must be followed by detailed reports when further information becomes available. Participants must be followed up until clinical recovery is complete, even if this is after the 28-day timeframe, and any laboratory or imaging results have returned to normal or baseline, or until the event has stabilized. Follow up information will be provided on an SAE report marked as such.

#### **10.4 CTRU responsibilities**

The Sponsor delegates CTRU responsibility for the reporting of SAEs to the regulatory authorities and the Research Ethics Committee (REC), as appropriate. CTRU will also keep all investigators informed of any safety issues that arise during the course of the study.

#### **10.5 SAE additional reporting**

The Data Monitoring and Ethics Committee (DMEC) and Trial Steering Committee (TSC) will also receive information on all AEs and SAEs, at a frequency agreed with each committee and documented in the appropriate charter/terms of reference.

### **11. Statistics**

#### **11.1 Sample size**

The sample size of 494 (247 per arm) was based on a non-inferiority margin of one point on the FLACC, an expected conservative standard deviation of 3.3, with a one-sided alpha of 0.025, and 90% power, 15% loss to follow-up and a conservative estimate of correlation with baseline FLACC values of 0.3.

The non-inferiority margin was chosen based on face-to-face meetings with parents of children who had previously sustained a toddler's fracture. Pain levels in general and the FLACC scale in particular were discussed. Parents were asked to identify what difference in score they felt would reflect a difference in treatments for toddler's fractures. There was universal agreement that they would consider alternatives to

immobilisation management for their toddler's fractures only if this did not increase pain by more than one point in the FLACC score.

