### **4. Trial Design**

A multicentre, prospective, parallel group, individually randomised (1:1), pragmatic, non-blinded controlled non-inferiority trial with 4 week follow up and within-trial health economic analysis.

The trial aims to recruit 494 participants and will be conducted in approximately 20 NHS Trusts, including specialist Children's Hospitals; Tertiary units that treat children and District General Hospitals. Participants will be primarily recruited in Emergency

Departments, and in Fracture clinics if required. Eligibility will be confirmed by the researcher and study information given. Parents/guardians will be given time to consider the interventions following receipt of information about the study. Written consent will be taken from parents/guardians after any questions have been addressed. Due to the young age of participants, assent will not be obtained. Participants whose parents/guardians have consented will be randomised to receive either immobilisation, or no immobilisation, then followed up for 28 days.

A 6-month internal pilot, with clear progression criteria to full trial (see section 8.3) will follow the recommendations of Avery et al, and assess the feasibility of site set-up and recruitment.

The internal pilot trial will use data from all sites which are open to recruitment within the first 6 months after the first site is opened. To allow time for collation of site and participant recruitment, and primary outcome, the progression criteria will be assessed by the Trial Steering Committee at the end of the following month. Data from the internal pilot will be included in the final analysis. At the end of the internal pilot phase, if any amber criteria are met, a recovery plan detailing remedial actions will be agreed with the Trial Steering Committee and submitted to the funder.

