### 8.3 Internal pilot outcomes

A 6-month internal pilot to assess feasibility of site set-up and recruitment (Table 1).

**Table 1:** Internal Pilot progression criteria

|                                                                                       | Red: Consider ending study if at least TWO criteria are met. | Amber: Proceed with protocol amendments and remediation, as agreed with TSC | Green: Proceed |
|---------------------------------------------------------------------------------------|---------------------------------------------------------------------|------------------------------------------------------------------------------------|-----------------------|
| No. of sites open and recruited 1st participant                                       | <60% (n<12)                                                         | $\geq 60\%$ (n=12-19)                                                              | 100% (n=20)           |
| No. of participants recruited                                                         | <60% (n<60)                                                         | $\geq 60\%$ (n=60-99)                                                              | 100% (n=100)          |
| Mean recruitment rate per site                                                        | <50% (<0.8)                                                         | 50-99% (0.8-1.62)                                                                  | 100% (1.63)           |
| Proportion of participants completed primary outcome measure of those who reached it* | <85%                                                                | 85-99%                                                                             | 100%                  |
| Adherence to allocated treatment**                                                    | <80%                                                                | 80-99%                                                                             | 100%                  |

\*The number of participants for whom primary outcome data are expected allows for time for follow-up visits to be reached, as well as for reminders to be sent and data to be processed, including return of paper questionnaires. Therefore, this data will only be included for participants who were randomised 10 days prior (if via text) or 40 days prior (if via paper) to the date that the data is extracted for the analysis.

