## **11.2 Statistical Analysis**

The trial will be analysed and reported according to Consolidated Standards of Reporting Trials (CONSORT) guidelines for noninferiority designs.

The primary endpoint, i.e. FLACC scores, will be analysed using a three-level mixed effects model with randomised treatment, follow-up time point (used as a categorical variable), randomised treatment by time point interaction, baseline FLACC score and minimisation variables as fixed effects, and the post-randomisation FLACC scores at 3 days, day 7 (primary) and day 28 (level 1) nested within participants (level 2), nested within sites (level 3), with random intercepts at level 2 and 3. We shall use restricted maximum likelihood estimation and assume an exchangeable correlation for the covariance structure between the random effects.

The model will be used to obtain the marginal treatment effect (non-immobilisation vs. immobilisation) at 7 days post randomisation. Non-inferiority will be rejected if the upper limit of the 95% confidence interval exceeds the non-inferiority margin of one point in either the as-randomised or per-protocol population. Treatment effects will also be presented for other timepoints.

Sensitivity analyses will assess the potential impact of missing data (including missing not at random scenarios), adherence to the randomised intervention (complier-average causal effects, if appropriate) and area-under-the-curve analyses to summarise cumulative pain over the follow-up. Consistency of treatment effects between important subgroups, including minimisation factors, will be explored.

Secondary endpoints will be analysed using comparable models for continuous and binary endpoints, as appropriate. Time to weight bear will be presented using summary statistics, and compared between groups using a Cox proportional hazards model, adjusted for randomisation factors.

(Serious) Adverse events (i.e. those not included in the secondary outcomes) will be presented descriptively.

Index of Multiple Deprivation (IMD) deciles will be derived from postcodes, and used to explore if treatment preferences and satisfaction differ across different IMD deciles.

Full details of all planned analyses and analysis populations will be collated in a pre-specified statistical analysis plan.

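### The 90% power in section 11.1 is that of the as-randomised analysis alone; the two-population rule in section 11.2 has less whenever participants leave the per-protocol set

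*Protocol*

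**What the plan says.** Protocol section 11.1 states: "The sample size of 494 (247 per arm) was based on a non-inferiority margin of one point on the FLACC". The other inputs are "an expected conservative standard deviation of 3.3", "a conservative estimate of correlation with baseline FLACC values of 0.3", and the error rates and attrition in "with a one-sided alpha of 0.025, and 90% power, 15% loss to follow-up". It makes no allowance for per-protocol exclusions and does not say which analysis the 90% belongs to.

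Section 11.2 sets the decision rule. Non-inferiority is rejected if the upper limit of the 95% confidence interval for the day 7 treatment effect "exceeds the non-inferiority margin of one point in either the as-randomised or per-protocol population". It leaves the details of the analysis populations to the statistical analysis plan.

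Two other places bear on how many children might leave the per-protocol set. Section 7.3 discourages a change of treatment but lets parents make one, and it defines non-adherence in each arm. In section 8.3, Table 1 has a row headed "Adherence to allocated treatment", with 100% as green, 80-99% as amber and below 80% as red.

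**The concern.** Two adjacent sections do not match. Section 11.1 sizes the trial for one successful comparison, while section 11.2 asks for two. Under that rule the per-protocol analysis is a second hurdle, not a sensitivity analysis. If the per-protocol set is the as-randomised set less some exclusions, it is smaller, and the chance of passing both tests cannot exceed the chance of passing the per-protocol test alone.

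The stake is the type II error of the primary conclusion. A reader of section 11.1 would take 10% as the chance of missing non-inferiority when the treatments are truly equal on pain. Under the rule as written that chance is larger by an amount the protocol does not report. The oversight committees and the funder will also judge pilot adherence without knowing what imperfect adherence costs in power.

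**Working it through.** **Inputs.** From section 11.1: margin 1 point, SD 3.3, correlation with baseline 0.3, one-sided alpha 0.025, power 90%, loss 15%, 247 per arm. From section 4: 1:1 allocation. The true difference is not stated; 0 is assumed, and it reproduces the stated size.

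**Step 1: reproduce 494.**
- Baseline-adjusted SD = 3.3 × √(1 − 0.3²) = 3.148.
- Normal approximation: n per arm = 2 × (1.960 + 1.2816)² × 3.148² / 1² = 208.3, so 209; 209/0.85 gives 246 per arm, 492 in total.
- With the t distribution, power is 89.97% at 209 per arm and 90.1% at 210, so 210 is the smallest size that works. Then 2 × 210 / 0.85 = 494.1, the stated 494.

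The stated size is thus correct for one comparison, with nothing left over for a second.

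**Step 2: power of the rule in section 11.2.** Evaluable per arm = 247 × 0.85 = 209.95, taken as 210. The standard error is 3.148 × √(2/210) = 0.3072, and 1/0.3072 = 3.255.
- As-randomised analysis: Φ(3.255 − 1.960) = Φ(1.295) = 90.2% by normal approximation.
- Per-protocol analysis, with a share p of evaluable children retained: Φ(3.255√p − 1.960).
- The per-protocol set is nested in the as-randomised set, so with exclusions unrelated to outcome the two estimates have correlation √p. Joint power is the bivariate normal probability that both tests succeed, Φ₂(1.295, 3.255√p − 1.960; √p).

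| Excluded per protocol | Per-protocol power alone | Joint power |
|---|---|---|
| 0% | 90.2% | 90.2% |
| 1% | 89.9% | 89.4% |
| 5% | 88.7% | 87.7% |
| 10% | 87.0% | 85.9% |
| 20% | 82.9% | 81.6% |

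A simulation with t-based confidence intervals (10,000 trials per scenario) gave joint power of 87.7%, 86.2% and 80.9% at 5%, 10% and 20% exclusion, in line with the table.

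**Step 3: how far other margins in the plan could offset this.**
- Completion of 95% instead of 85%, other inputs unchanged: joint power 91.1% at 5% exclusion, 89.5% at 10%, 85.9% at 20%.
- SD 3.0 instead of 3.3, with 85% completion: 91.8% at 10% exclusion, but below 89% at 20%.
- Correlation 0.5 instead of 0.3, with 85% completion: 91.8% at 10% exclusion, but below 89% at 20%.

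**The case against.** The strongest reply is that nothing in section 11.1 is miscalculated: the listed inputs give 494, and the section never claims that 90% is the joint probability under section 11.2. That stands. A reader might infer that the sample size is wrong, but the documents do not support it. What is incomplete is the statement of what the 90% refers to.

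A reader might also infer that the design cannot deliver 90%. That goes too far, because the shortfall depends on an exclusion rate the protocol does not give. The only adherence target it names is 100%, at which single and joint power coincide, and at 1% exclusion the loss is under one point.

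Nor can it be taken as fact that every non-adherent child leaves the per-protocol set. Section 7.3 defines non-adherence, but section 11.2 leaves the populations to the statistical analysis plan, which is not at hand.

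The amber band is not a planning assumption either. Amber means proceeding with amendments and remediation agreed with the steering committee, and section 4 adds a recovery plan for the funder. The 81.6% figure combines the bottom of the amber adherence band with 85% completion, the bottom of the amber completion band. It is an unfavourable scenario, not an expected one.

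Finally, section 11.1 calls the SD and correlation conservative, sections 9 and 9.6 plan reminders, and the repeated-measures model can use day 3 and day 28 scores from children missing day 7. These are genuine possible reserves, although the protocol does not quantify the gain from the model. They do not remove the mismatch, because the 90% is quoted on the conservative inputs and has to be judged on them. Requiring success in both populations also does not raise the risk of a false claim of non-inferiority; the cost falls on power alone.

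**Conclusion.** The mismatch between sections 11.1 and 11.2 holds. The 90% is the power of the as-randomised analysis; the joint rule has less whenever participants are excluded from the per-protocol set. On the protocol's own inputs the joint type II error is about 12% at 5% exclusion, 14% at 10% and 18% at 20%, against the stated 10%.

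These sizes assume a true difference of 0 in both populations, exclusions unrelated to outcome, the stated SD and correlation, and 85% completion. A larger true difference against no immobilisation among adherent children would lower joint power further; better completion or more favourable inputs would raise it. At 5-10% exclusion the gap is 2 to 4 points and could be recovered; at 20% recovery would need a larger departure from the stated inputs. The point should be fixed, but it does not undermine the margin, the analysis or the sample size.

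**What to change.** Keep 494 and the decision rule. In section 11.1, state that 90% power refers to the as-randomised analysis. Then give the joint power for the per-protocol exclusion rate the team expects, with a range (for example 5-20%, about 88% down to 82% on the present inputs) and the assumptions: true difference 0, exclusions unrelated to outcome, 15% loss. The expected rate should match the per-protocol definition in the statistical analysis plan.

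The cost is a sentence or two and a slightly less favourable stated power; no further participants are needed. For scale, sizing for 90% joint power with 15% loss would take 532 participants at 5% exclusion, 564 at 10% and 630 at 20%, that is 38, 70 and 136 more than planned. That is not needed to correct the statement.

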## **11.2 Statistical Analysis**

The trial will be analysed and reported according to Consolidated Standards of Reporting Trials (CONSORT) guidelines for noninferiority designs.

The primary endpoint, i.e. FLACC scores, will be analysed using a three-level mixed effects model with randomised treatment, follow-up time point (used as a categorical variable), randomised treatment by time point interaction, baseline FLACC score and minimisation variables as fixed effects, and the post-randomisation FLACC scores at 3 days, day 7 (primary) and day 28 (level 1) nested within participants (level 2), nested within sites (level 3), with random intercepts at level 2 and 3. We shall use restricted maximum likelihood estimation and assume an exchangeable correlation for the covariance structure between the random effects.

The model will be used to obtain the marginal treatment effect (non-immobilisation vs. immobilisation) at 7 days post randomisation. Non-inferiority will be rejected if the upper limit of the 95% confidence interval exceeds the non-inferiority margin of one point in either the as-randomised or per-protocol population. Treatment effects will also be presented for other timepoints.

Sensitivity analyses will assess the potential impact of missing data (including missing not at random scenarios), adherence to the randomised intervention (complier-average causal effects, if appropriate) and area-under-the-curve analyses to summarise cumulative pain over the follow-up. Consistency of treatment effects between important subgroups, including minimisation factors, will be explored.

Secondary endpoints will be analysed using comparable models for continuous and binary endpoints, as appropriate. Time to weight bear will be presented using summary statistics, and compared between groups using a Cox proportional hazards model, adjusted for randomisation factors.

(Serious) Adverse events (i.e. those not included in the secondary outcomes) will be presented descriptively.

Index of Multiple Deprivation (IMD) deciles will be derived from postcodes, and used to explore if treatment preferences and satisfaction differ across different IMD deciles.

Full details of all planned analyses and analysis populations will be collated in a pre-specified statistical analysis plan.

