|---------------------------------------------------------|---------------------------------------------------------------------------------------------------------------------------------------------------------------------------------------------------------------------------------------------------------------------------------------------------------------------------------------------------------------------------------------------------------------------------------------------------------------------------------------------------------------------------------------------------------------------------------------------------------------------------------------------------------------------------------------------------------------------------------------------------------------------------------------------------------------------------------------------------------------------------------------------------------------------------------------------------------------------------------------------------------------------------------------------------------------------------------------------|
|                                                         | 
 
Planned and unplanned attendances to ED, plaster room, or fracture clinics
 
Use of plain radiograph imaging on the affected limb since randomisation
 
Occurrence of and treatment for pressure ulcers, resulting from the use of immobilisation
 
Occurrence of and secondary intervention for fracture displacement
 
 
Collected via parent/guardian questionnaires:
 
 
Pain (via FLACC scale or Revised FLACC) at 3 days and 28 days post randomisation.
 
Recovery of pre-injury mobility (time to weight bear) (asked at 3 days, 7 days and 28 days if mobility was not recovered by previous timepoint)
 
Requirement for and type of oral analgesia up to day 7 (asked at 3 days and 7 days)
 
Resource use and contact with General Practitioners since randomisation (asked at 28 days)
 
Satisfaction with allocated treatment (asked at 28 days)
 
Removal of immobilisation (asked at 3 days, 7 days and 28 days)
 
 |

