## **7.3 Treatment adherence**

Treatment change will be discouraged. Sites will discuss with parents/guardians the importance for the trial of remaining in their allocated treatment and will establish equipoise before the patient is randomised. However, if a parent/guardian still does wish to change their child's treatment after randomisation they can do so.

For participants randomised to the immobilisation arm, non-adherence is defined as follows:

- Removing the immobilisation prior to the 7th day after fitting (inclusive, i.e., up until the end of the 7th day),
- Not receiving any immobilisation by day 3 after initial presentation

For participants randomised to the non immobilisation arm, non-adherence is defined as follows:

- Receiving any new immobilisation before the 7th day after randomisation (inclusive, i.e. up until the end of the 7th day).
- Not removing any immobilisation fitted prior to randomisation by day 3 after initial presentation

Information on all immobilisation received during the will be recorded, including fitting/removal dates (from medical records/parent questionnaires), and the reason for change where available.

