## 8.2 Secondary outcomes/endpoints

Collected via medical note review by site staff at 28 days post randomisation:

- Planned and unplanned attendances to ED, plaster room, or fracture clinics
- Use of plain radiograph imaging on the affected limb since randomisation.
- Occurrence of and treatment for pressure ulcers, resulting from the use of immobilisation.
- Occurrence of and treatment for fracture displacement.

Collected via parent/guardian questionnaires:

- Pain (via FLACC scale or Revised FLACC) at 3 days and 28 days post randomisation.
- Recovery of mobility (time to weight bear) (asked at 3 days, 7 days and 28 days post randomisation if mobility was not recovered by previous timepoint).
- Requirement for and type of oral analgesia up to day 7 (asked at 3 days and 7 days).
- Resource use and contact with GPs since randomisation (asked at 28 days post randomisation).
- Satisfaction with allocated treatment assessed by Likert Scale and open question (asked at 28 days post randomisation).
- Removal of immobilisation (asked at 3 days, 7 days and 28 days)

These timepoints are based on the minimal risk of long-term problems with these injuries and associated pain not persisting beyond 4 weeks due to healing.

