| Parent/ guardian Satisfaction                        |                |          |           |         |                      | Q         |
| Attendances at ED, Plaster Room, or Fracture clinics |                |          |           |         |                      | MR        |
| X-rays on affected limb                              |                |          |           |         |                      | MR        |
| Pressure ulcers/ fracture displacement               |                |          |           |         |                      | MR        |
| Removal of immobilisation                            |                |          |           | Q       | Q **                 | Q ** / MR |
| Safety                                        |                |          |           |         |                      |           |
| Adverse events                                       |                |          |           |         |                      | MR***     |

S = data collected in person/remotely by site staff

Q = data collected from parent/guardian via a self-completion questionnaire

MR = data collected from medical records

\*post randomisation

\*\*if not recovered/removed at previous timepoint

\*\*\*Adverse events followed up until no longer ongoing

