## **9.6 Loss to contact**

Efforts will be made to contact parents/guardians, and questionnaires will be sent, for all follow-up timepoints, regardless of whether the parent/guardian has completed questionnaires at the previous time point. Two text message reminders will be sent per questionnaire time-point (at one and two days after the initial questionnaire is sent), plus a phone call reminder for the day 7 questionnaire, or paper questionnaires, if required. Questionnaires will be open for completion until the end of the trial. Date of completion will be collected and considered for the analysis. Questionnaires will close two weeks after the 28 day follow-up timepoint for the last recruited participant.

After the study closes, participants will be defined as lost to contact if no questionnaire data is available for one follow-up time point, and all subsequent stipulated follow-up time points.

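### Section 11.2 fixes a plain Cox model for time to weight bear, although recovery is asked only at days 3, 7 and 28 and no date of first weight bearing is said to be recorded

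*Protocol*

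**What the plan says.** Protocol section 8.2 lists recovery of mobility, with time to weight bear in brackets, as a secondary outcome from the parent questionnaires, "asked at 3 days, 7 days and 28 days post randomisation if mobility was not recovered by previous timepoint". The schedule in section 9.1 repeats the skip rule in a footnote: "if not recovered/removed at previous timepoint". Participants are "randomised to receive either immobilisation, or no immobilisation, then followed up for 28 days", so day 28 is the last look.

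Section 11.2 names the method: summary statistics, and a comparison between the arms, "compared between groups using a Cox proportional hazards model, adjusted for randomisation factors". It mentions neither ties nor interval censoring. Its closing sentence says: "Full details of all planned analyses and analysis populations will be collated in a pre-specified statistical analysis plan".

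Two other places bear on the point. Section 7.3 says that all immobilisation is recorded, "including fitting/removal dates (from medical records/parent questionnaires"; no matching statement exists for weight bearing. Section 9.6 says: "Questionnaires will be open for completion until the end of the trial. Date of completion will be collected and considered for the analysis".

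The event itself has two descriptions. Section 1.6 has "Recovery of pre-injury mobility (time to weight bear", while section 8.2 leaves out the reference to pre-injury level.

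**The concern.** A Cox model needs an event time for each child. The Protocol establishes only three occasions on which recovery is asked about, the last two 21 days apart. If the answer is a yes or no, the recovery time is known only to lie between the last 'no' and the first 'yes'. Using the questionnaire day as the event time puts every event at one of three values. The estimated hazard ratio then depends on how the software handles ties, and it is drawn toward 1 under either common method.

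Recovery time is named in the second aim (section 3.1), and the rationale (section 2.2) expects quicker recovery without immobilisation. Immobilisation is meant to last at least 7 days and ideally 2 weeks (section 7.1). Recovery after its removal would therefore often fall in the widest interval.

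The two event descriptions matter separately. Section 2.2 says that a child can still bear weight while immobilised. Such a child may be weight bearing but not back to pre-injury mobility, so the choice of event could change the comparison between arms however times are captured.

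**Working it through.** The Protocol gives no figure for this outcome, so there is none to reproduce.

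**Inputs.** From the Protocol: looks at days 3, 7 and 28 (section 8.2), follow-up to day 28 (section 4), 1:1 allocation, and 247 per arm with 15% loss (section 11.1), which leaves 247 × 0.85 ≈ 210 analysed per arm. Assumed, because the Protocol gives none: exponential recovery times, control medians of 3 to 21 days, and true hazard ratios of 1.0, 1.5 and 2.0.

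**Status-only data, large sample.** Let r0 and r1 be the proportions not yet recovered at the start of an interval (control, no immobilisation), d0 and d1 the proportions recovering in it, d = d0 + d1, and θ the fitted hazard ratio.

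- Breslow: Σ d1 = Σ d · r1θ / (r0 + r1θ).
- Efron: as Breslow, but with r0 − s·d0 and r1 − s·d1 in place of r0 and r1, averaged over s from 0 to 1.

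Example with control median 7 days and true hazard ratio 1.5. The control proportion not recovered at day t is exp(−t·ln 2/7), and the other arm's is that value to the power 1.5.

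| Interval | r0 | r1 | d0 | d1 |
|---|---|---|---|---|
| (0,3] | 1.0000 | 1.0000 | 0.2570 | 0.3596 |
| (3,7] | 0.7430 | 0.6404 | 0.2430 | 0.2869 |
| (7,28] | 0.5000 | 0.3536 | 0.4375 | 0.3379 |

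The left side is 0.3596 + 0.2869 + 0.3379 = 0.984. At θ = 1.258 the Breslow right side is 0.6166 × 0.5571 + 0.5299 × 0.5202 + 0.7754 × 0.4708 = 0.984. So the Breslow estimate is 1.26 where the truth is 1.5. The Efron equation gives 1.40.

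| Control median (days) | True 1.5: Efron | True 1.5: Breslow | True 2.0: Efron | True 2.0: Breslow |
|---|---|---|---|---|
| 3 | 1.39 | 1.24 | 1.78 | 1.43 |
| 5 | 1.38 | 1.25 | 1.74 | 1.47 |
| 7 | 1.40 | 1.26 | 1.75 | 1.48 |
| 10 | 1.43 | 1.28 | 1.80 | 1.51 |
| 21 | 1.48 | 1.35 | 1.93 | 1.64 |

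At a true hazard ratio of 1.0 both methods return 1.0.

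**Simulation at the trial's size** (210 per arm, 300 replicates, medians 3 to 21 days, true hazard ratio 1.5):

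| Data and ties | Estimate | Power |
|---|---|---|
| Status only, Breslow | 1.23 to 1.36 | 61 to 79% |
| Status only, Efron | 1.38 to 1.49 | 91 to 96% |
| Day recorded, Efron | 1.49 to 1.52 | 92 to 99% |
| Day recorded, Breslow | 1.41 to 1.50 | 92 to 98% |

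**Does the alternative work?** Under proportional hazards, ln(1 − p1)/ln(1 − p0) equals the hazard ratio in every interval, where p is the probability of recovering in the interval given no recovery before it. In the example, (0,3] gives ln 0.6404 / ln 0.7430 = 1.50. Complementary log-log regression uses this relation. In 100 replicates it returned 1.49 (median 5 days) and 1.50 (median 10 days) for a true 1.5, and 2.01 (median 5 days) for a true 2.0.

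**The case against.** A reader might infer that recovery is observed only at three times, that the plan treats those times as exact, and that bias toward no difference is therefore certain. The documents do not support that. Section 8.2 says when the question is put, not what answer is taken. The outcome is called time to weight bear, which fits a form that asks when. Removal of immobilisation follows the same questionnaire days and shares the same footnote in section 9.1, and for that item section 7.3 does record dates. This makes a reported date plausible without establishing it, and the questionnaires are not shown. If the day is recorded, Cox with Efron ties is essentially unbiased, and forcing the data into three intervals would throw information away. That part of the objection stands, and the point is conditional because of it.

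It would also go too far to say that a child with a missed early form is counted as recovering later. Section 9.6 keeps forms open, sends reminders and retains the completion date, and no derivation rule is given.

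The other argument is that ties and event-time derivation belong in the statistical analysis plan. For tie handling alone that would be fair. But section 11.2 has already chosen the model, and that choice suits one form of data and not the other. Whether it suits this outcome cannot be settled from the Protocol.

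**Conclusion.** The point holds as a conditional one. The Protocol fixes plain Cox for an outcome asked about on three days, without saying that a date is recorded. If only status is known, the hazard ratio is pulled toward 1: modestly with Efron ties (a true 1.5 becomes 1.38 to 1.48) and substantially with Breslow (1.24 to 1.35). For a true 2.0 the ranges are 1.74 to 1.93 and 1.43 to 1.64. These ranges rest on exponential times and control medians of 3 to 21 days, both assumed.

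The limits are clear. There is no bias under no true effect, and with Efron ties it is negligible if the day is recorded. The outcome is secondary, so the day 7 pain comparison and the sample size of 494 are untouched. The mismatch between pre-injury mobility, mobility and weight bearing exists whichever way times are captured.

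**What to change.** - In section 11.2, state whether parents report the date of first weight bearing.
- Replace plain Cox by a proportional-hazards model for interval-censored data. It should use the reported date where one is given and otherwise the interval from the last 'no' to the first 'yes'.
- If only status is collected, use discrete-time complementary log-log regression, which estimates the same hazard ratio.
- If all dates are collected, keep Cox and specify Efron ties.
- Report the proportions recovered by day 7 and by day 28 in each arm, with 95% confidence intervals.
- Reconcile sections 1.6 and 8.2 so that one event is defined and analysed.

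The cost is a change of wording in the Protocol and the statistical analysis plan, and standard software. No new data are needed.
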